## Abstract

**Background:**

Eczema is a chronic, relapsing skin condition commonly managed by emollients and topical corticosteroids. Prevalence of use and demand for effective botanical therapies for eczema is high worldwide, however, clinical evidence of benefit is limited for many currently available botanical treatment options. Robustly-designed and adequately powered randomised controlled trials (RCTs) are essential to determine evidence of clinical benefit. This protocol describes an RCT that aims to investigate whether a mānuka oil based emollient cream, containing 2% ECMT-154, is a safe and effective topical treatment for moderate to severe eczema.

**Methods:**

This multicentre, single-blind, parallel-group, randomised controlled trial aims to recruit 118 participants from community pharmacies in Aotearoa New Zealand. Participants will be randomised 1:1 to receive topical cream with 2% ECMT-154 or vehicle control, and will apply assigned treatment twice daily to affected areas for six weeks. The primary outcome is improvement in subjective symptoms, assessed by change in POEM score. Secondary outcomes include change in objective symptoms assessed by SCORAD (part B), PO-SCORAD, DLQI, and treatment acceptability assessed by TSQM II and NRS.

**Discussion:**

Recruitment through community pharmacies commenced in January 2022 and follow up will be completed by mid-2023. This study aims to collect acceptability and efficacy data of mānuka oil based ECMT-154 for the treatment of eczema. If efficacy is demonstrated, this topical may provide an option for a novel emollient treatment. The community-based design of the trial is anticipated to provide a generalisable result.

**Ethics and dissemination:**

Ethics approval was obtained from Central Health and Disability Ethics Committee (reference: 2021 EXP 11490). Findings of the study will be disseminated to study participants, published in peer-reviewed journal and presented at scientific conferences.

**Trial registration:**

Australian New Zealand Clinical Trials Registry (ANZCTR) ACTRN12621001096842. Registered on August 18, 2021 (https://www.anzctr.org.au/Trial/Registration/TrialReview.aspx?id=382412&isReview=true).

**Protocol version:**

2.1 (Dated 18/05/2022).

## Background

Eczema is a common, chronic or recurrent inflammatory skin condition, characterised by acute flares of pruritic lesions [1, 2]. Although prevalence is highest in children, for many it can persist into, or even develop in, adulthood [3–6]. Aotearoa New Zealand has a high prevalence of disease, with Māori and Pacific populations having a greater disease burden than New Zealand Europeans [7, 8]. Eczema represents a significant individual and societal financial burden, and contributes to a strain on healthcare resources [9–11]. Additionally, patient quality of life is significantly affected due to persistent itch, pain, disturbance of sleep, and emotional distress [12, 13].

Eczema is caused by complex interactions of genetics, environmental factors, and immune activation [14, 15]. The primary mechanisms for the pathophysiology include skin barrier dysfunction and immune dysregulation [16, 17]. Filaggrin is a key protein in epidermal barrier function, preventing water loss and entry of allergens and infectious organisms [18]. Two common loss-of-function mutations in the gene encoding Filaggrin can lead to an epidermal barrier defect, and have been strongly linked to the development of eczema [19, 20]. This reduction of epidermal integrity can cause allergen and microbe introduction, leading to activation of the immune system and inflammatory response [21]. The immune response in patients with eczema is associated with CD4^+^ T cells (Th) and upregulated expression of Th2 and Th22 cytokines, resulting in chronic inflammation [22–24].

Skin colonisation by *Staphylococcus aureus (S. aureus)* is common among patients with eczema, at a carriage rate much higher than the general population [25–27] *S. aureus* is associated with disease pathogenesis, and symptom flares which can result in loss of skin microbiota diversity, further allowing *S. aureus* to dominate which can lead to significant secondary infections [28–30].

There is currently no cure for eczema, treatment instead focuses on symptom management, including identification and avoidance of irritants that exacerbate symptoms [31–33]. The primary strategy for symptom management includes the regular use of emollients to maintain and restore skin barrier function [34]. Topical corticosteroids or calcineurin inhibitors effectively reduce inflammation and are often used to treat symptom flares, or used prophylactically to maintain disease control [32, 33, 35]. However, up to 80% of eczema patients report fears around topical corticosteroids use, with concerns of side effects leading to low treatment adherence, a major contributing factor in treatment failure, and consequent poor disease control [36–38].

Prevalence of use and demand for plant-derived botanical therapies for eczema is high worldwide, [39, 40] however high quality clinical evidence for the efficacy of such products is limited. ECMT-154 is a formula comprising β-triketone rich mānuka oil and palmarosa oil, both of which demonstrate anti-inflammatory and antimicrobial activity [41–44]. In vitro, mānuka oil reduces lipopolysaccharide-induced release of inflammatory cytokine TNF-α [41]. The geraniol component of palmarosa oil has also demonstrated inhibition of various inflammatory pathways in vitro and in vivo [42, 45–47]. β-triketone rich mānuka oil and geraniol are also both effective agents against gram-positive bacteria, such as *S. aureus* [44, 48–50]. The anti-inflammatory effects may be effective in relieving eczema symptoms when lesions develop while anti-staphylococcal activity may be beneficial by reducing eczema severity and lower the risk of secondary infections. This randomised controlled trial (RCT) is designed to investigate whether in vitro evidence may translate to clinical benefit, through reduction of symptoms in patients with eczema.

This study aims to assess efficacy of a novel, non-steroidal topical emollient cream containing 2% ECMT-154 via an RCT in community pharmacies.

## Methods and analysis

### Study design

This study is a parallel-group, superiority, assessor-blinded RCT assessing the efficacy of 2% ECMT-154 compared with vehicle control in the topical treatment of moderate to severe eczema in adults. The trial protocol has been developed in accordance with Standard Protocol Items: Recommendations for Interventional Trials (SPIRIT) guidelines [51].

### Trial setting and recruitment

This study will be conducted using the Medical Research Institute of New Zealand (MRINZ) Pharmacy Research Network (PRN), an established network of over 80 research trained community pharmacists in Aotearoa New Zealand overseen centrally by researchers at the MRINZ [52, 53]. Between 10–15 pharmacies will recruit participants and undertake study related procedures. Pharmacies were selected based on previous recruitment success and capacity to complete study procedures. Adults presenting to a PRN pharmacy seeking advice for eczema will be screened for eligibility. Advertising within participating pharmacies and on mainstream or social media will be used as a recruitment tool.

### Screening and selection

An anonymous pre-screening survey will be available for potential participants to self-screen against eligibility criteria (Table 1). At the pharmacy participants will be screened using a predefined statement to determine suitability for the study, followed by anonymised assessment of Patient Oriented Eczema Measure (POEM) score [54]. If participants decline participation or do not meet the inclusion criteria of POEM score (≥ 8 to ≤ 24), no further information will be collected. Moderate to severe eczema is required to prevent a floor effect, and increase the likelihood of detecting a significant change in POEM score. Willing participants provide written informed consent, and undergo assessment of eligibility.

**Table 1 Tab1:** Eligibility criteria

Inclusion criteria	• Participant is willing and able to provide written informed consent • Participant is aged between 18 and 65 years, inclusive • Participant reported, doctors diagnosis of eczema • Patient has a representative eczema lesion, located below the clavicle that is in an area they are comfortable having photographed • Patient has a POEM score of ‘moderate to severe eczema’ (8 to 24) • Participant is willing to stop all moisturisers and other skin barrier cream or emulsion during the treatment period and replace it with the investigational product assigned in this trial. Usual facial regimens and application of sunscreen is permitted • Participant is willing to replace their body wash/soap with aqueous cream as supplied at enrolment • Participant is able to attend a follow up visit six weeks after they enrol in the study. This will take place at a participating pharmacy or via telephone call if required due to COVID restrictions or unanticipated inability to attend in person • Participant is willing and able to comply with the study and comply with all study procedures
Exclusion criteria	• Current requirement for antibiotics or corticosteroids for the treatment of any condition (with the exception of inhaled and intranasal corticosteroids) • Use of topical and/or oral antibiotics, corticosteroids, or antihistamines within the last two weeks (with the exception of inhaled and intranasal corticosteroids) • Use of immunomodulatory medications taken for eczema within the past four weeks • Cutaneous mycotic or bacterial disease requiring a topical or systemic therapy • Other skin condition which may affect the assessment of eczema • History of allergy or hypersensitivity to study treatment ingredients • Participation in a clinical study involving an investigational product during the last three months • Participant is pregnant/breastfeeding or planning to become pregnant during the study • Cold/flu like symptoms, fever, or unexplained shortness of breath in the past 14 days • Any other condition which, at the investigators’ discretion, is believed may present a safety risk or impact upon the ability of the participant to complete the study

### Randomisation and masking

Participants are randomised 1:1 to receive a 2% ECMT-154 cream or vehicle control. Participants will be block randomised, block size four, and randomisation will be stratified according to site. A computer-generated randomisation number sequence will be created by the study statistician. Randomisation of participants takes place at the pharmacy, electronically within REDCap. Participants will be randomised by pharmacy investigators who have no access to the randomisation schedule. Manufacturing and labelling of interventional treatments will be conducted by an external compounding pharmacist, licensed to complete such activities and assessed according to Good Manufacturing Practice guidelines. Active treatment and vehicle control will be labelled as “Treatment G” and “Treatment H” in non-descript packaging for the purpose of blinding. Study investigators at the pharmacies and MRINZ will be blinded. Participants will not be told if they receive the active or control cream, however due to the distinctive smell of ECMT-154 compared to control, participants are assumed to be unblinded therefore this study will conservatively be classified as single blind rather than double blind.

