### Participant timeline

Upon presentation to the pharmacy, consent, demographic data, eligibility, and baseline data are collected, followed by a clinical photograph of a representative eczema lesion, chosen by the participant. The participant is randomised, and the appropriate treatment is dispensed by the study pharmacist along with the aqueous cream. Over the six-week interventional period, participants complete a weekly digital diary to report POEM, treatment adherence, adverse events, and use of concomitant medications (Table 2). Participants return to the pharmacy for a second face to face visit at week six including a second clinical photograph of the representative lesion. A final electronic follow up survey is completed at week eight to collect any adverse events following the cessation of study treatment. The study flow is depicted in Fig. 1*.*

**Table 2 Tab2:** Summary of study procedures

	Visit 1	Treatment Period					Visit 2	Follow Up Survey
Day	**0**	**7**	**14**	**21**	**28**	**35**	**42 (+ 5)**	**14 days post Visit 2 (+ 5)**
Eligibility screen	X							
Informed consent	X							
Demographic data collection	X							
POEM	X	X	X	X	X	X	X	
PO-SCORAD	X						X	
SCORAD (Part B)	X						X	
DLQI	X						X	
Eczema photo	X						X	
Randomisation	X							
Dispense medication	X							
Electronic study diary		X	X	X	X	X		
Treatment compliance		X	X	X	X	X	X	
Adverse event collection		X	X	X	X	X	X	X
TSQM Version II							X	
Acceptability NRS							X

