### Trial status

At the time of submission, participant recruitment began in January 2022. Enrolment is anticipated to continue through to mid-2023. Current protocol version 2.1 dated 18th May 2022.

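### A fixed block of four within each pharmacy and two shared treatment letters let a pharmacist foresee up to a third of the letters, and decoding one letter turns this into knowledge of treatment

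*Protocol article*

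**What the plan says.** All the elements are in the protocol article.

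- **Allocation** (Randomisation and masking): "Participants are randomised 1:1 to receive a 2% ECMT-154 cream or vehicle control". The blocks are fixed and run within site: "Participants will be block randomised, block size four, and randomisation will be stratified according to site". Pharmacy investigators randomise electronically in REDCap and cannot see the schedule.
- **Labelling** (same section): "Active treatment and vehicle control will be labelled as “Treatment G” and “Treatment H” in non-descript packaging for the purpose of blinding". This is one code per arm, and nothing suggests that the codes differ between pharmacies.
- **Masking** (same section): investigators at the pharmacies and at the coordinating institute are to be blinded. Participants are presumed to know their arm because the active cream smells different from the control.
- **Dispensing** (Participant timeline): consent, eligibility, baseline data and randomisation belong to the first pharmacy visit, where "the appropriate treatment is dispensed by the study pharmacist along with the aqueous cream".
- **Sites** (Trial setting and recruitment): "Between 10–15 pharmacies will recruit participants and undertake study related procedures".
- **Outcomes** (Outcome measures): the primary outcome is self-reported POEM. SCORAD part B, scored by the pharmacist, is secondary.

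**The concern.** Withholding the schedule conceals allocation only if the schedule cannot be worked out. Here each pharmacy has its own sequence of blocks, and the letter of every tub is visible on handover. A pharmacy's own dispensing history is therefore its complete allocation sequence so far. With a known block size, the end of each block follows by subtraction.

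The shared letters add a second weakness. Once someone learns what G is, H is known too, and so is the arm of everyone whose letter that person has seen or can foresee.

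Two things are at stake:

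- **Selection at enrolment.** Eligibility includes judgement: willingness and ability to comply, and a catch-all exclusion left to the investigator. Both are exercised before randomisation. Someone who can foresee the treatment could, knowingly or not, apply them differently. This could reach the primary comparison, and adjustment for baseline POEM does not remove selection on unmeasured prognosis.
- **Assessment.** The article describes the trial as assessor-blinded. Pharmacist-scored SCORAD part B depends on that, as does the comparison of pharmacist with dermatologist scores, both of whom are described as blinded.

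**Working it through.** **Inputs.** Block size 4, ratio 1:1, blocks within site, two letters (Randomisation and masking); 10 to 15 pharmacies (Trial setting and recruitment); 118 participants (Power calculation). The article gives no figure for predictability.

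**The plan's own figure.** The total of 118 is used here only to size the sites. For a difference of 3.4, SD 6.0 and two-sided 5% alpha, 50 per arm gives 80.1% power (noncentral t). Then 50 / 0.85 = 58.8, rounded up to 59 per arm, or 118. The figure is reproduced.

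**Step 1: one completed block.** The six orders of GGHH are equally likely. An allocation is certain when only one letter is left in the block.

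| Position in block | P(next letter certain) | P(best guess right) |
|---|---|---|
| 1 | 0 | 1/2 |
| 2 | 0 | 2/3 |
| 3 | 1/3 (first two alike) | 2/3 |
| 4 | 1 | 1 |

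- Certain: (0 + 0 + 1/3 + 1) / 4 = 33.3%.
- Best guess right: (1/2 + 2/3 + 2/3 + 1) / 4 = 70.8%, against 50% by chance.

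**Step 2: incomplete last blocks.** 118 / 15 = 7.9 and 118 / 10 = 11.8, so pharmacies enrol about 8 to 12 each if recruitment is even. The expected number of certain letters is:

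- 8 participants: 2 × 4/3 = 2.67, or 33.3%
- 9 participants: 2.67, or 29.6%
- 10 participants: 2.67, or 26.7%
- 11 participants: 2.67 + 1/3 = 3, or 27.3%
- 12 participants: 3 × 4/3 = 4, or 33.3%

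Over these sizes the best guess is right 68% to 71% of the time.

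**Step 3: whole trial, even recruitment.**

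- 10 pharmacies (eight with 12, two with 11): 8 × 4 + 2 × 3 = 38 certain, or 32.2%.
- 12 pharmacies (ten with 10, two with 9): 12 × 2.67 = 32 certain, or 27.1%.

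Across 10 to 15 pharmacies the range is 32 to 38 of 118. With uneven recruitment (an assumed Dirichlet spread of site sizes) the mean is 28% to 30%.

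**Step 4: from letter to treatment.** Steps 1 to 3 concern letters. Before decoding, knowing that G comes next gives no reason to favour or avoid a patient. After decoding, the same percentages apply to treatments, and all letters already seen are unmasked. The documents give no probability of decoding.

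**Step 5: what varying blocks achieve.** Sizes equally likely, order hidden, 8 to 12 participants per pharmacy:

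| Block sizes | Certain | Best guess right |
|---|---|---|
| 4 (plan) | 27% to 33% | 68% to 71% |
| 2, 4, 6 | about 3% | 67% to 69% |
| 4, 6, 8 | about 2% to 3% | 65% to 67% |

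Varying the blocks nearly abolishes certainty but hardly reduces guessing, so it cannot be the whole remedy.

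**The case against.** The strongest reply is that fixed blocks of four are a common choice and that the harm needs several conditions at once. The pharmacist must know the block size, track the letters and decode one of them. The article speaks of pharmacy investigators in the plural. It does not say that the person dispensing also scores SCORAD at week six, or that tubs are opened at the pharmacy. Baseline data are collected before randomisation, the POEM entry range is numeric, and the primary analysis adjusts for baseline POEM. The pharmacist's SCORAD is one of many secondary outcomes and is compared with a remote dermatologist's score.

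Much of this stands and makes the risk conditional. It does not remove it. Tracking letters for 8 to 12 participants is easy, the article states the block size, and participants presumed to know their arm return to the pharmacy in person. Baseline adjustment covers measured severity, not discretionary exclusion.

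A reader might infer more than the documents support:

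- *That a third of treatments are known in advance.* Only letters are, until one is decoded.
- *That central staff, or those classifying adverse events and protocol deviations, are unblinded too.* The article does not say that they see letters, and it describes the coordinating institute's investigators as blinded.
- *That the block size became public while recruitment was open.* The article says only, as at submission, "Enrolment is anticipated to continue through to mid-2023". It gives no publication date.
- *That assessment of the primary outcome is compromised further.* POEM is self-reported by participants already presumed to know their arm.

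**Conclusion.** The point holds as a design vulnerability, not as evidence that prediction or unblinding took place. Lack of access to the schedule does not secure concealment when 27% to 33% of letters can be deduced at pharmacies of 8 to 12 participants. Two shared letters make pharmacist blinding depend on no one ever linking a letter to the smell.

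The percentages assume that the pharmacist knows the block size and sees every letter at the site, and that recruitment is roughly even. Their reading as treatments further assumes one decoded letter. The reach of a decoded letter is limited to participants whose letter that person has seen, normally one pharmacy.

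For POEM the added risk is selection at enrolment. For SCORAD part B it is also assessment bias. With participants presumed unblinded, the masking of assessors is the main masking left, so it merits a change if allocations remain to be made.

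**What to change.** For allocations still to be made:

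1. **Main change.** Have REDCap issue a participant-specific tub number in place of letters G and H. A disclosure then reveals one participant's arm and not a whole site's, and the visible code no longer carries the block pattern.
2. **Supporting change.** Have the statistician generate new site lists with randomly varying block sizes, for example 4, 6 and 8, not disclosed to the pharmacies.

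If enrolment has closed, report the limitation and compare baseline characteristics between predictable and unpredictable block positions.

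**Cost.** Relabelling of undispensed stock at 10 to 15 pharmacies (two tubs of study cream per participant), a new list upload, a protocol amendment, and slightly looser balance within site. The gain shrinks as enrolment nears completion. Numbering cannot mask the smell for an individual participant.

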### Interventional treatments

Study intervention, and vehicle control are expected to provide emollient benefits from ingredients in the base cream, comprised of polyethylene glycol (300 and 3350), water, white soft paraffin, stearyl alcohol, propylene glycol, and sodium lauryl sulphate. Treatments are identical in formulation, with the exception of 2% ECMT-154 added to interventional cream. Participants will be dispensed two 500 gram tubs of study treatment for liberal application to affected areas twice daily, morning and night, for six weeks. In addition, three 500 gram tubs of aqueous cream (Boucher, India) will be supplied to replace participants usual soap and body wash. Adherence to randomised treatment will be collected in weekly diaries with participants asked how many times they used their treatment each day over the past week.

### Participant timeline

Upon presentation to the pharmacy, consent, demographic data, eligibility, and baseline data are collected, followed by a clinical photograph of a representative eczema lesion, chosen by the participant. The participant is randomised, and the appropriate treatment is dispensed by the study pharmacist along with the aqueous cream. Over the six-week interventional period, participants complete a weekly digital diary to report POEM, treatment adherence, adverse events, and use of concomitant medications (Table 2). Participants return to the pharmacy for a second face to face visit at week six including a second clinical photograph of the representative lesion. A final electronic follow up survey is completed at week eight to collect any adverse events following the cessation of study treatment. The study flow is depicted in Fig. 1*.*

**Table 2 Tab2:** Summary of study procedures

	Visit 1	Treatment Period					Visit 2	Follow Up Survey
Day	**0**	**7**	**14**	**21**	**28**	**35**	**42 (+ 5)**	**14 days post Visit 2 (+ 5)**
Eligibility screen	X							
Informed consent	X							
Demographic data collection	X							
POEM	X	X	X	X	X	X	X	
PO-SCORAD	X						X	
SCORAD (Part B)	X						X	
DLQI	X						X	
Eczema photo	X						X	
Randomisation	X							
Dispense medication	X							
Electronic study diary		X	X	X	X	X		
Treatment compliance		X	X	X	X	X	X	
Adverse event collection		X	X	X	X	X	X	X
TSQM Version II							X	
Acceptability NRS							X

